#### NSP intensity

To determine NSP intensity, the subjects are asked through a questionnaire to mark a vertical line on the VAS line at the point which represents their pain intensity in each area (i.e., head, neck, shoulder, and upper back) on a scale ranging from 0 to 10 representing no pain and severe, respectively [71, 72].

#### Workability and sick leave due to pain

Workability is self-assessed using the related questionnaires by a single validated item from the workability index [73, 74]. The subjects respond to one question as to how they rate their current workability according to their capabilities to meet the mental and physical demands of their job, which can still perform in two years. The response scores range from 0 to 10, indicating inability to work and workability with a cut-off point score of ≤7 implying poor workability, respectively [75]. In addition, sick leave due to pain is evaluated using a single item from the validated Outcome Evaluation Questionnaire to obtain data on the number of absence days from work due to pain in muscles or joints within the past month, and response categories ranged from 0 to 31 days [76]. Based on a recent meta-analysis, self-reported sick leave demonstrates good reliability and validity against the records [77].

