**Methods and design:**

To this end, 45 subjects within the age range of 30–45 years are randomly assigned to three groups in the present parallel-group, randomized control trial using a pretest-posttest design. These groups include the subjects who receive online-supervised exercise and workplace exercise containing three sessions of intervention for 8 weeks and the control group receives no intervention while performing routine activities. The primary outcome variables are neck-shoulder pain (NSP) and consequent sick leave due to NSP, followed by alignment, workability, and the surface electromyography of upper, middle, and lower trapezius (UT, MT, and LT), sternocleidomastoid (SCM), and serratus anterior (SA) as the secondary variables.

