### Objectives

Given the explanations mentioned earlier, the present study seeks to evaluate the effect of workplace-based versus online-supervised home-based corrective exercises containing NSP and sick leave due to NSP as the primary objectives.

The secondary objectives include workability, alignment (i.e., neck, shoulder, and thoracic spine angles), and assessing the surface EMG of designated muscles including UT, MT, LT, SCM, and SA among office workers with UCS.

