### Outcome measures

Before randomization and at baseline, all assessments are performed and repeated after the intervention. NSP and sick leave due to pain are considered as the primary outcome variables, followed by the alignment, workability, and electromyography (EMG) activities of the selected muscles as the secondary variables. In the first part of the questionnaire, the subjects are asked to insert their demographic and social status including gender, age, weight, and height (body mass index = kg/m^2^), work hour/week, years of experience, education level, and marital status [71].

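### The primary outcome named as sick leave due to neck-shoulder pain is measured by an item that counts absence for muscle or joint pain at any site

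*Protocol article*

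**What the plan says.** The protocol article describes this outcome in four places.

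- **Abstract, Methods and design:** "The primary outcome variables are neck-shoulder pain (NSP) and consequent sick leave due to NSP".
- **Objectives:** the comparison is described as "containing NSP and sick leave due to NSP as the primary objectives".
- **Outcome measures, opening paragraph:** "NSP and sick leave due to pain are considered as the primary outcome variables". No site is attached to the sick leave here.
- **Workability and sick leave due to pain:** "sick leave due to pain is evaluated using a single item from the validated Outcome Evaluation Questionnaire", which records the "number of absence days from work due to pain in muscles or joints within the past month"; "response categories ranged from 0 to 31 days".

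On timing, Outcome measures says that "all assessments are performed and repeated after the intervention", so the item is answered at baseline and once after the 8-week programme.

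**The concern.** Two places tie the outcome to the neck and shoulder, one leaves the site open, and the item covers muscles and joints in general. Followed as written, the plan produces a count of absence days for musculoskeletal pain at any site and reports it against an objective about NSP.

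This affects one of only two primary outcomes. The Intervention section describes exercises aimed at the neck, shoulder and thoracic muscles, so the question is whether absence caused by pain in that region changes. With the item alone, a difference between groups could come from NSP days, from days lost to other pain, or from both. A null result could also hide an NSP effect behind unrelated absence. With 15 subjects per group, there is little room for avoidable noise.

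**Working it through.** No stated figure decides this point, so the check is mainly a comparison of texts, followed by a short look at what the extra days do to the analysis.

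**1. Label against instrument**

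| Place | Cause of absence |
|---|---|
| Abstract | NSP |
| Objectives | NSP |
| Outcome measures | pain, site not given |
| Item description | muscle or joint pain, site not given |

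The article does not leave the item's content to another document. It states the content, and that content is wider than the objective. This is an inconsistency and not an omission.

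**2. Does anything else narrow the item to the neck and shoulder?**

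- *Rewording:* nowhere is the item said to be adapted or restricted.
- *Eligibility:* subjects need a pain score of at least 3 in the neck and shoulder. Musculoskeletal pain elsewhere is not excluded unless it prevents exercise. Entry criteria therefore do not make all-site absence equal to NSP absence.
- *Validation:* the article calls the questionnaire validated and says self-reported sick leave agrees well with records. Neither statement shows that the item isolates a neck or shoulder cause.
- *Contrast:* the pain scale is marked separately for head, neck, shoulder and upper back. The plan separates regions for pain but not for sick leave.

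**3. What the other-site days do**

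Write Y = A + B, where A is days lost to NSP and B is days lost to other muscle or joint pain.

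- *Difference in means:* Δ(Y) = Δ(A) + Δ(B). If the programme leaves B unchanged, randomisation makes Δ(B) = 0 in expectation, so Δ(Y) = Δ(A). If the programme also changes B, Δ(Y) mixes the two, and the item cannot show which case applies.
- *Variance:* Var(Y) = Var(A) + Var(B) + 2 Cov(A, B). This exceeds Var(A) unless A and B are strongly negatively related. The same absolute difference is then estimated less precisely.
- *Proportional change:* suppose a share s of reported days is due to NSP and the programme halves only those days. The item then shows a reduction of 0.5 × s. The document supplies neither s nor the halving, so the range is illustrative only:

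| s | reduction shown by the item |
|---|---|
| 0.3 | 15% |
| 0.5 | 25% |
| 0.7 | 35% |
| 0.9 | 45% |
| 1.0 | 50% |

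**4. Link to the sample size**

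The stated 11 per group is reproduced if the effect size of 0.66 is read as Cohen's f with two groups, alpha 0.05 and target power 0.80. Power is 0.797 at n = 10 and 0.837 at n = 11. The article does not state the metric, so this reading is an assumption. It ties that effect size to neck pain, so the calculation does not concern sick leave and the mismatch leaves it unchanged.

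**The case against.** **The operational sections already fit the item.** Outcome measures and the heading above the item both speak of sick leave due to pain, so the drift lies in the abstract and objectives. This stands, and it means that renaming would remove the inconsistency. It does not make the inconsistency disappear, because the objective that the trial sets out to answer is still worded as NSP.

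**The item includes NSP absence.** This also stands. A reader might infer that the item fails to measure the stated outcome at all. The text does not support that; the item is broader than the label.

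**Other-site days cancel in a randomised comparison.** Largely true. The Statistical method section compares means by ANOVA and by ANCOVA with the pre-test as covariate. If the programme does not affect other-site absence, the difference in days is not diluted, and the covariate removes part of any stable other-site absence. What remains is added noise and loss of attribution.

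**A reader might infer a large loss of power.** If 40 to 60% of days were due to NSP and relative variability were unchanged, the required sample size would rise by 1/s², from 1/0.6² = 2.8 to 1/0.4² = 6.3 times. The document supports neither assumption. If A and B were independent with equal relative variability, the factor would be 1 + ((1 − s)/s)², which is 1.44 at s = 0.6 and 3.25 at s = 0.4. The share may also be higher in people selected for neck and shoulder pain. No multiplier can be defended from this text.

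**A reader might also fault the one-month recall,** because at post-test it reaches back over only about half of the 8 weeks. The window is clearly stated and is the same at both assessments. Measuring the last month, after exposure has built up, is a reasonable choice and not an error.

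**Conclusion.** The mismatch is real and rests on the text alone. The abstract and objectives promise a result on sick leave due to NSP, while the item yields sick leave due to musculoskeletal pain at any site. A result on the item could be read as an NSP effect only by assuming that absence for other pain does not change with the programme, and the planned data cannot test that.

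The cost is noise of unknown size plus a limit on attribution. It is not systematic bias in the comparison of groups, and it does not call the sample-size figure into question. It should be corrected because it concerns a primary outcome and the correction is small.

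**What to change.** Keep the validated item and add one question at baseline and post-test: *of these days, how many were because of neck or shoulder pain?* The NSP objective can then be assessed directly, with the all-site count reported beside it. The protocol should say that the added question is unvalidated and that subjects who know whether they exercise are attributing the days themselves, so expectation may colour the answers. For that reason it is debatable whether it should replace the validated item as the primary measure.

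If baseline data have already been collected without the question, use the name *sick leave due to musculoskeletal pain* in the Abstract, Objectives and Outcome measures, and limit the conclusion to that outcome.

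The question itself costs one line per assessment. The Randomization section requires a formal amendment agreed by the registry and approved by the Ethics Committee for changes to objectives or procedures, so the administrative cost is more than a note. Trial status puts the study at subject enrolment, with recruitment expected from December 2020 to June 2021. Whether any baseline answers already exist should therefore be settled first.

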#### Alignment

To determine the angles for forward head and round shoulder postures, visible landmarks are placed on the ear tragus, the acromion process of the scapula, and the neck seventh vertebra process, as well as the 12th dorsal vertebra of the spinous for measuring the kyphosis angle, respectively [78]. Further, photogrammetry is utilized, asking the subjects to stand laterally and comfortably with bare feet on the flat floor while looking forward. A digital camera is fixed at a distance of 265 centimeters from the subjects, and then three photos are taken from the lateral view [79]. Furthermore, the angles are identified using AutoCAD software (version 2020) connecting a vertical line from the tragus to C7 for determining forward head and continuing to the acromion process for displaying the rounded shoulder angles. To identify the thoracic kyphosis angle, C7 and T12 markers are considered as the starting and ending points of the arch. Previous research indicted the photogrammetry intrarater and interrater reliability ICC 0.98–0.99 and ICC 0.91–0.99 respectively [78, 80–82]. Finally, the mean of three measurements is considered as the alignment angle.

#### EMG

The onset timing and amplitude for the dominant side of the selected muscles (i.e., UT, MT, LT, SCM, and SA) are recorded using EMG, and Matlab software is applied for data analysis [83]. After preparing the skin, electrodes are placed according to the European protocol of SENIAM^2^, and then the reference electrode for each muscle is attached to the nearest bony site of the muscle. Additionally, a maximum voluntary isolated contraction (MVIC) is used to normalize and standardize the data by the root of the mean square (RMS). In addition, the subjects are requested to elevate their hand 30° in the scapular plate without any resistance in three phases (i.e., isometric, concentric, and centric) five times with a 3-s break within each repetition. Then, the mean RMS is calculated based on three of five repetitions, followed by divining the mean RMS by the MVIC value multiplied by 100 to obtain the percentage of muscle activity [84]. The reliability of this method was observed within-day (0.85–0.99) and between-day (0.68–0.93) intraclass correlation coefficient for normalized RMS activity and within-day (0.94 ) and between-day (0.80) intraclass correlation coefficient for time broadness respectively [85, 86].

### Sample size

Based on the results of the previous studies and a pilot study, 11 subjects are calculated for each group using G*Power software (version 3.0.10, Germany) with an alpha level of 0.05, power (1 − β) of 80%, and effect size of 0.66. It should be noted that the effect size was reported in the previous study that investigated the effects of corrective exercises on neck pain between the intervention and control groups [41]. However, to avoid the probability of losing the subjects during the research process, the number is considered 15 in every three groups (*N* = 45 subjects).

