### Statistical method and analysis

Data are analyzed using IBM SPSS statistics software, version 24 for Windows, and descriptive statistics are applied to describe the variables considering sig. ≤0.05. Further, data normality is reported based on the Shapiro-Wilk test.

A 3 (group) × 2 (time) mixed-model repeated-measures ANOVA is used to compare all values from the pre-test to each point of the time within each group. Furthermore, the mixed-model repeated-measures ANOVA is applied to analyze within-group changes. Additionally, Bonferroni’s post hoc test for indicating the significance is utilized for any significant difference, and one-way ANCOVA is employed to compare the groups in the post-test with each pre-test value as a covariate. In addition, the effect size is calculated for the magnitude of the difference using the partial *η*2 method as small (0.01 ≤ *η*2 < 0.06), medium (0.06 ≤ *η*2 < 0.14), or large (*η*2 ≥ 0.14). It should be noted that interim analyses were not planned in the present study.

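### The 11 per group cannot be matched to the three-group design: it is far too few if 0.66 is a standardised mean difference, and enough for the overall test if it is Cohen's f

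*Protocol article*

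**What the plan says.** The Sample size section of the protocol article reports that "11 subjects are calculated for each group using G*Power software" "with an alpha level of 0.05, power (1 − β) of 80%, and effect size of 0.66". It attributes the 0.66 to an earlier study that "investigated the effects of corrective exercises on neck pain between the intervention and control groups". To allow for losses, "the number is considered 15 in every three groups", giving 45 in total.

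The section does not say whether 0.66 is Cohen's d, Cohen's f or another measure. It also does not give the G*Power test, the number of groups entered, whether the test is one- or two-sided, or a pre-post correlation.

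The trial has three groups (Study design). The Statistical method and analysis section plans a 3 × 2 mixed ANOVA and a one-way ANCOVA on the post-test with the pre-test as covariate. It adds a Bonferroni "post hoc test for indicating the significance is utilized for any significant difference". It names partial eta-squared for reporting the size of effects in the results.

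**The concern.** The article gives the inputs, the software and the result, so a reader should be able to get from one to the other. An effect published for an intervention group against a control group is most naturally a standardised mean difference. With d = 0.66, groups of 11 are far too small for 80% power.

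What is at stake is how a non-significant result is read. If 80% power is taken at face value, a null pairwise comparison looks like an adequately powered negative, whereas on the d reading the chance of detecting the planning effect is well under one half without baseline adjustment. The title question, workplace against online-supervised exercise, is the most exposed, because the planning effect comes from a different contrast.

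**Working it through.** **Inputs from the protocol article.** Effect size 0.66, alpha 0.05, power 80%, 11 per group raised to 15 (Sample size); three groups (Study design); equal allocation (Randomization). Alpha is taken as two-sided. Correlations are assumptions, since the article gives none.

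**1. Reproducing 11.** For a one-way F test with k groups of n, λ = f² × k × n on (k − 1, kn − k) degrees of freedom.

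- k = 2, f = 0.66, n = 11: λ = 0.66² × 22 = 9.58, power 83.7%. With n = 10, power is 79.7%. So this gives exactly 11. With two groups d = 2f, so the effect is d = 1.32.
- k = 3, f = 0.66: n = 8 gives 77%, n = 9 gives 83%. The three-group answer is 9 per group.
- Three-group by two-time interaction, f = 0.66, assumed r = 0.5: 4 per group.
- Eta-squared = 0.66, so f = √(0.66/0.34) = 1.39, three groups: 3 per group.

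Repeated-measures interaction runs starting from d = 0.66 can also reach 11. Here λ = f² × N × 2/(1 − r).

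- Two groups, f = d/2 = 0.33, r = 0.5: λ = 0.33² × 22 × 2/0.5 = 9.58, so 11 per group, numerically the same calculation as the first.
- Three groups, f = 0.33, r = 0.35: 11 per group (81%; 77% at 10).
- Three groups, f = 0.311, r = 0.45: 11 per group (83%; 79% at 10). This f comes from means 0, 0.66, 0.66 SD: f = 0.66 × √2/3.

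These need a correlation that the article does not state, and entering d/2 as the interaction f is doubtful. With equal baselines and a post-test difference of 0.66 SD in two groups, the interaction f is 0.66/4 = 0.165. Then λ = 0.165² × 22 × 2/0.5 = 2.40 and power at 11 per group is 31%.

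**2. If 0.66 is d.** Two-sample t test, noncentrality d√(n/2) on 2n − 2 degrees of freedom.

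- n = 37 gives 79.98%, n = 38 gives 81.0%: 38 per group. One-sided: 30. At alpha 0.05/3 = 0.0167: 50.
- n = 11: 0.66 × √5.5 = 1.55, power 31%. n = 15: 0.66 × √7.5 = 1.81, power 42%.
- At alpha 0.0167: 17% and 25%.

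Baseline adjustment enlarges the effect to d/√(1 − r²):

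| Assumed r | Adjusted d | n = 11 | n = 15 |
|---|---|---|---|
| 0.5 | 0.76 | 40% | 52% |
| 0.7 | 0.92 | 54% | 69% |
| 0.8 | 1.10 | 69% | 83% |

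These are at alpha 0.05. At r = 0.8 with alpha 0.0167 they are 50% and 68%. Reaching 80% with 11 per group at alpha 0.05 needs r of about 0.85.

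**3. If 0.66 is f.** Three-group omnibus test: λ = 0.66² × 33 = 14.4, power 91% at 11 per group; λ = 0.66² × 45 = 19.6, power 98% at 15.

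One Bonferroni pair at alpha 0.0167, taking d = 2 × 0.66 = 1.32: 68% at 11 and 85% at 15. In three groups the pairwise d depends on the pattern of means. With two equal exercise groups against control, d = 0.66 × 3/√2 = 1.40, and the same formula gives 74% at 11.

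**The case against.** A reader might infer that 11 is a plain arithmetic error and that the trial therefore lacks its stated power. The article does not support that. The metric is unnamed and the source study is not available here. G*Power takes f for its ANOVA tests, and the planned analyses are ANOVA and ANCOVA. On that reading 11 per group is a surplus over the 9 needed, with 91% omnibus power, or 98% if all 15 are retained. Nor is the two-group F test the only route to 11: the repeated-measures runs above reach it, some with three groups.

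The Bonferroni criticism can also be pressed too far. The power statement is not tied to a pairwise test, and sizing on the overall test at 0.05 is common. If 0.66 is f, a corrected pair has 85% power at the enrolled 15, and baseline adjustment would raise the 68% at 11. A condensed article may also leave the software settings to the full protocol.

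All of this stands against a flat claim of error. It does not make the paragraph sound. The direct calculation giving 11 leaves out one of the three groups. The others rely on an undisclosed correlation and a doubtful conversion. The article itself prints inputs, result and power as a set, and that set points to sample sizes from 3 to 38 per group depending on what 0.66 means.

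**Conclusion.** The concern holds in conditional form. The stated inputs do not lead to 11 per group for the three-group design without something the article leaves unsaid.

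- **If 0.66 is d**, the more natural reading of its source, the 80% figure is not met at either sample size for an unadjusted pairwise comparison. Baseline adjustment rescues it only with 15 retained and a correlation near 0.8, before Bonferroni.
- **If 0.66 is f**, the overall test is well powered. The shortfall is confined to Bonferroni-corrected pairs at 11 per group without baseline adjustment.

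On either reading, the unadjusted, Bonferroni-corrected pair falls below 80% at the calculated 11. An effect of exercise against control gives no basis for expecting an equal difference between two exercise programmes, so no power claim for workplace versus online exercise follows from it. It cannot be concluded from the article that the trial as a whole has less than 80% power. These results assume a two-sided alpha, and the adjusted ones rest on assumed correlations of 0.5 to 0.8.

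**What to change.** Keep N = 45 and rewrite the Sample size paragraph.

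1. State whether 0.66 is d or f, and give the G*Power test, number of groups, pre-post correlation and alpha that were entered.
2. Rerun the calculation for the three-group design.
3. Replace the 80% statement with the power, or the smallest detectable difference, for the omnibus test and for one Bonferroni-adjusted, baseline-adjusted pairwise comparison, each at 11 and at 15 per group.
4. Say that the planning effect is exercise against control and was not derived for workplace versus online exercise.
5. If 0.66 is d, withdraw the 80% claim and state that a non-significant pairwise result is not evidence of no difference.

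The cost is wording in the protocol and registry. No recruitment target changes. The drawback is that the stated power becomes less favourable.

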### Statistical method and analysis

Data are analyzed using IBM SPSS statistics software, version 24 for Windows, and descriptive statistics are applied to describe the variables considering sig. ≤0.05. Further, data normality is reported based on the Shapiro-Wilk test.

A 3 (group) × 2 (time) mixed-model repeated-measures ANOVA is used to compare all values from the pre-test to each point of the time within each group. Furthermore, the mixed-model repeated-measures ANOVA is applied to analyze within-group changes. Additionally, Bonferroni’s post hoc test for indicating the significance is utilized for any significant difference, and one-way ANCOVA is employed to compare the groups in the post-test with each pre-test value as a covariate. In addition, the effect size is calculated for the magnitude of the difference using the partial *η*2 method as small (0.01 ≤ *η*2 < 0.06), medium (0.06 ≤ *η*2 < 0.14), or large (*η*2 ≥ 0.14). It should be noted that interim analyses were not planned in the present study.

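### At N = 45 the partial eta-squared bands label most null three-group results at least small and most significant ones large, so they are a poor statement of magnitude

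*Protocol article*

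**What the plan says.** The protocol article's section Statistical method and analysis plans a 3 (group) × 2 (time) mixed ANOVA, Bonferroni post hoc tests, and an ANCOVA: "one-way ANCOVA is employed to compare the groups in the post-test with each pre-test value as a covariate". On size, "the effect size is calculated for the magnitude of the difference using the partial" eta-squared, read off as "small (0.01 ≤ *η*2 < 0.06), medium (0.06 ≤ *η*2 < 0.14), or large (*η*2 ≥ 0.14". Values below 0.01 have no label. This is the only rule for magnitude in the text. It is not limited to particular outcomes, and the text does not say which of the planned effects it grades.

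The significance level is 0.05 ("descriptive statistics are applied to describe the variables considering sig. ≤0.05"). The section Sample size calculates 11 per group "with an alpha level of 0.05", "power (1 − β) of 80"% and an "effect size of 0.66". To allow for losses, "the number is considered 15 in every three groups", which makes 45. No dropout rate is given.

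**The concern.** Sample partial eta-squared cannot be negative, and its expected value under no effect depends on the residual degrees of freedom. With 45 people in three groups, that chance level already lies well inside the small band, so a label of small, and often medium, will attach to outcomes on which nothing happened. At the other end, the value needed for significance almost equals the large cut. Most significant three-group results are then called large, whether the true effect is small or substantial.

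The index also has no direction and pools all three groups, whereas the stated question is workplace versus online-supervised exercise. The Abstract and Discussion offer the findings as evidence for employers, and the Abstract also for clinicians. A large label that mostly restates p ≤ 0.05 invites an overstatement of benefit.

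**Working it through.** **Inputs.** Bands 0.01, 0.06 and 0.14, and level 0.05 (Statistical method and analysis). N = 45, and 3 × 11 = 33 as the calculated size before the allowance for losses (Sample size). Treating 33 as the number of completers is an assumption. For the three-group effect df1 = 2. The residual df2 is N − 3 for the group × time interaction (42 or 30) and N − 4 for the ANCOVA with one covariate (41 or 29).

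**The plan's own figure.** With f = 0.66, two groups, level 0.05 and 80% power, the noncentral F gives 11 per group (power 0.837; 10 per group gives 0.797). So 11 reproduces if 0.66 is read as f in a two-group comparison. In variance-explained terms, f = 0.66 is 0.66²/(1 + 0.66²) = 0.4356/1.4356 = 0.303.

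**Under no effect.** Partial eta-squared = 2F/(2F + df2). With df1 = 2 it follows Beta(1, df2/2), so the mean is 2/(2 + df2) and P(value ≥ c) = (1 − c)^(df2/2). The smallest significant value is 1 − 0.05^(2/df2).

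| | N = 45, interaction (42) | N = 45, ANCOVA (41) | N = 33, interaction (30) | N = 33, ANCOVA (29) |
|---|---|---|---|---|
| Mean | 2/44 = 0.045 | 2/43 = 0.047 | 2/32 = 0.063 | 2/31 = 0.065 |
| P(small or more) | 0.99^21 = 0.810 | 0.99^20.5 = 0.814 | 0.99^15 = 0.860 | 0.99^14.5 = 0.864 |
| P(medium or more) | 0.94^21 = 0.273 | 0.94^20.5 = 0.281 | 0.94^15 = 0.395 | 0.94^14.5 = 0.408 |
| P(large) | 0.86^21 = 0.042 | 0.86^20.5 = 0.045 | 0.86^15 = 0.104 | 0.86^14.5 = 0.112 |
| Smallest significant value | 0.133 | 0.136 | 0.181 | 0.187 |

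At N = 45 the share of significant null results labelled large is 0.0421/0.05 = 84% (interaction) or 0.0454/0.05 = 91% (ANCOVA). At N = 42 or fewer the smallest significant value exceeds 0.14 (0.142 and 0.146 at 42), so the share is 100%.

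**Under a true effect.** F is noncentral with λ = N·η²/(1 − η²). For the ANCOVA at N = 45:

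| True η² | below small | small | medium | large | large, given significant |
|---|---|---|---|---|---|
| 0 | 0.186 | 0.533 | 0.236 | 0.045 | 0.91 |
| 0.03 | 0.100 | 0.408 | 0.344 | 0.149 | 0.94 |
| 0.10 | 0.020 | 0.167 | 0.357 | 0.456 | 0.96 |
| 0.14 | 0.007 | 0.086 | 0.281 | 0.626 | 0.97 |
| 0.303 (f = 0.66) | 0.000 | 0.002 | 0.026 | 0.973 | 1.00 |

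For the interaction the last column reads 0.84, 0.89, 0.94, 0.955 and 0.995.

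**One-df effects at N = 45** (a pairwise contrast, or time). P(small or more) under no effect is about 0.52. The smallest significant value is 0.088–0.090 unadjusted, and 0.129–0.132 with Bonferroni over three pairs.

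**Omega-squared as an alternative.** Partial omega-squared = 2(F − 1)/(2(F − 1) + N). At N = 45, untruncated, its mean is about 0.00 under no effect and 0.058 when the truth is 0.06. If negative values are set to zero, the null mean rises to 0.017. Its smallest significant value is (2 × 2.226)/(2 × 2.226 + 45) = 0.090 for the ANCOVA, and when the truth is 0.06 its mean among significant results is 0.156.

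**The case against.** The strongest reply is that the labels are descriptive and conventional, fixed in advance and free of contradiction. No success rule, error rate or sample size uses them, and significance is judged separately. A reader who sees p = 0.6 beside a small label is not misled. That no decision depends on the bands stands, and it confines the harm to reporting. It does not rescue the rule, which is a stated choice and the only statement of magnitude in the text.

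Four stronger readings are tempting, and the documents do not support them.

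- *The bands cannot discriminate at all.* They can: large occurs in 4–5% of null trials and 97% of trials at f = 0.66. It is the lower bands that overlap.
- *86% of null results are labelled at the planned size.* At 45 the figure is 81%. The 86% needs 33 completers, and the article states no dropout rate.
- *Every significant difference is large.* This is shown for the three-group test. The text does not tie the bands to that test, and for an unadjusted one-df effect a significant medium result is common.
- *Omega-squared cures the problem.* It removes nearly all of the average bias if left untruncated. It does not remove the inflation among significant results, which any estimator shows in a small trial filtered by p. At fixed N it too is a monotone function of F.

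One might also say that confidence intervals are detail which an article leaves to a fuller plan. That would be fair if the article were silent on magnitude, but it fixes a rule and the rule grades badly.

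**Conclusion.** The point holds for the three-group test. At N = 45, 81% of null results are labelled small or more and 27–28% medium or more. About 84–91% of significant results under no effect, and 89–97% at true values of 0.03–0.14, are labelled large. With 33 completers the null figures would be 86% and 40–41%, and every significant three-group result would be large. A true value of 0.03 is called small only about 41% of the time, and a true value of 0.10 is called medium only about 36% of the time.

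These figures assume normal errors, equal groups and grading of the two-df effect. For a skewed outcome such as sick-leave days they are approximate. The consequence is misread magnitude, not a wrong error rate or sample size. The change is worth making because it is cheap.

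**What to change.** In Statistical method and analysis, drop the partial eta-squared bands as the statement of magnitude. For each outcome, report the three baseline-adjusted mean differences from the planned ANCOVA (workplace vs online, workplace vs control, online vs control) in the outcome's own units, such as VAS points, each with a 95% confidence interval. If a variance-explained index is kept, report partial omega-squared untruncated, with its confidence interval and without small/medium/large labels. Note beside it that it reduces the average bias but not the inflation among significant results.

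The cost is a wording change. The adjusted means and intervals come from the same ANCOVA, omega-squared is one line of arithmetic from F, and no new data or participants are needed. The downside is that reported effects will look smaller and less certain.
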